### Intervention

Both interventions consist of eight group sessions conducted weekly in 120-min sessions (Fig. 1).

#### Mindful Yoga Program

This intervention consists of eight 120-min weekly group sessions led by a certified yoga instructor who has extensive experience in teaching yoga techniques to medical patients. The Mindful Yoga Program is based in part on the Kripalu school of yoga, which is widely taught in the U.S. [45, 46]. Mindful Yoga can be distinguished from many current yoga styles in that it places strong emphasis on developing mindfulness via substantial meditation practice, breathing exercises, study of yoga philosophy, practitioner meetings, and informal application of mindful awareness in daily life [26]. Mindfulness entails strategies for developing greater moment-to-moment presence of mind, along with acceptance of and willingness to learn from stressful experiences, so as to begin to recognize clearly what choices contribute to more wellbeing versus suffering [39, 47, 48]. Accordingly, during posture exercises Mindful Yoga intensively highlights the inner dimensions of practice—such as nonreactive monitoring of sensory, mental and emotional fluctuations—along with proper alignment and breathing techniques. The yoga instructor follows a detailed intervention manual ([name], [name]: Mindful Yoga Professional Training Manual, unpublished). Each session includes gentle postures (approx. 40 min), breathing techniques (10 min), meditation (25 min), presentations on the application of yogic principles to optimal coping (e.g., mind/body stress reactions; 20 min), and group discussions (e.g., experiences during meditation; 25 min). The yoga poses included in this protocol carry no more risk of injury than everyday activities such as climbing stairs. They have been specifically selected and tailored to meet the needs of women with MBC, and the instructor emphasizes gentle performance. Patients are supplied with yoga mats, eye pillows, and bolsters for doing poses. Participants are encouraged to practice yoga techniques at home, 15–30 min per day, 5–6 days per week, guided by professionally produced video recordings. Participants also receive brief session summary handouts each week, which include instructions for the informal application of yoga practice to daily life (e.g., in-the-moment acceptance of pain).

#### Social support comparison condition

This intervention consists of eight 120-min weekly group sessions led by a licensed clinical social worker experienced in leading groups and in working with patients with advanced cancer. The scheduling of the sessions is identical to that for the yoga intervention. The social support intervention is modeled after the protocol utilized by Breitbart and colleagues, and the therapist follows a detailed treatment manual [35]. The sessions focus on discussion of issues and themes that emerge for patients coping with MBC, including the following: coping with medical tests; communicating with healthcare providers; coping with family and friends; vocational issues; body image and physical functioning concerns; fears about future physical or psychological changes, recurrence, and mortality; and plans for the future. Utilizing a supportive approach, the therapist focuses on encouraging patients to share concerns related to the cancer diagnosis and treatment, to describe their experiences and emotions related to these experiences, to voice problems that they have in coping with cancer, and to offer support and advice to other group members.

### Measures

All participants complete assessments at baseline, post-treatment, and 3-month and 6-month follow-up (see Table 1). In addition, they complete daily diary measures during alternating weeks during the intervention period assessing symptoms and yoga practice (for those in the yoga condition).

**Table 1 Tab1:** Sequence of trial measurements for primary and secondary outcomes

	Pre-Screening	Telephone Screening	Baseline	Treatment	Mid-Treatment	Treatment	Post-Treatment	3-Month Follow-up	6-Month Follow-up
VISIT, Time (weeks)	(-16-0)	(-13-0)	1 (-4–0)	2–4 (1–3)	5 (4)	6–9 (6–8)	10 (9)	11 (21)	12 (34)
Primary outcome measures									
Attendance at intervention sessions				X		X			
Client Satisfaction Questionnaire-8							X		
Secondary outcome measures									
Brief Pain Inventory-Short Form			X				X	X	X
Brief Fatigue Inventory			X				X	X	X
Pittsburg Sleep Quality Index			X				X	X	X
Hospital Anxiety & Depression Scale			X				X	X	X
Mindfulness questionnaire (FFMQ-SF)			X				X	X	X
Complementary/alternative medicine use			X				X	X	X
6-min Walk Test			X				X	X	X
Medical record review	X		X				X	X	X
ECOG or KPS	X								
Demographics			X						
Daily diary items				X		X			
Medication log			X		X		X	X	X
Health questionnaire			X						
Treatment expectations			X		X				
Adverse events			X	X	X	X	X	X	X

#### Attendance

Attendance and time spent at each session are recorded by having participants sign in and out of each session, including the precise time at which they enter and leave. The interventionist verifies the times recorded.

#### Satisfaction with intervention

This is assessed with the 8-item Client Satisfaction Questionnaire-8, a briefer version of the larger Client Satisfaction Questionnaire [49]. This measure is frequently used to assess participants’ satisfaction with, and impression of the effectiveness of, the services they received. Items are rated on a four-point scale. This measure has good reliability (alpha coefficient = .93). It is administered at the post-treatment assessment only.

#### Pain

Pain is assessed with the Brief Pain Inventory-Short Form, a 9-item self-report measure that assesses worst, least, and average levels of pain and the degree which pain interferes in activities, mood, relationships, sleep, and enjoyment of life. This measure is widely used with cancer patients, has evidence of reliability and validity, and is considered the preferred method of assessing pain endpoints [50, 51].

#### Fatigue

The Brief Fatigue Inventory assesses self-reported levels of current, worst, and usual fatigue, and interference due to fatigue. The measure consists of 9 items on which respondents choose a number from 0 to 10 to rate each item on the scale. Factor analysis has shown that 75% of the variance on the Brief Fatigue Inventory can be explained by a single factor suggesting that it measures a single construct. This measure has also shown good evidence of concurrent and discriminant validity as well as excellent internal consistency (alpha = .96.) [52].

#### Sleep quality

Sleep quality is assessed by the Pittsburgh Sleep Quality Index, a 19-item self-report measure that produces a total sleep quality score and seven sleep component scores [53]. Higher scores indicate poorer sleep quality. The scale has been widely used with breast cancer patients with internal consistency for the total scale reported as .78 [54].

#### Psychological distress

The Hospital Anxiety and Depression Scale (HADS) is used to assess depression and anxiety symptoms. The HADS is a 14-item, 2-domain (depression and anxiety) scale with evidence of reliability, validity, and responsiveness among cancer patients [55, 56]. Domain scores ≥ 8 indicate either likely depression or anxiety.

#### Mindfulness

The Five Facet Mindfulness Questionnaire-Short Form (FFMQ-SF) assesses different aspects of mindfulness [57]. The FFMQ-SF is a 24-item short form of the Five Facet Mindfulness Questionnaire, a comprehensive measure for assessing mindfulness [58]. The FFMQ-SF has demonstrated reliability and validity as well as sensitivity to change in samples of adults with anxiety and depression as well as fibromyalgia [57].

#### Functional capacity

Patients’ functional capacity is assessed by the 6-min Walk Test administered in a measured corridor according to American Thoracic Society (ATS) guidelines [59]. Patients are instructed to walk at their fastest pace and to cover the longest possible distance over 6 min. This test has been shown to be a reliable and sensitive measure of functional capacity in deconditioned clinical populations and a sensitive test to assess therapeutic response. The test has been successfully used in several prior studies of cancer patients, including patients with advanced disease, with no adverse events [60]. This test has been shown to be a strong predictor of all-cause mortality in lung cancer patients [61].

#### Daily pain, fatigue, positive mood, negative mood, pain catastrophizing, and pain acceptance

Daily variation in pain, fatigue, positive mood, and negative mood is each assessed with a single 0-9 scale item. Similar numeric scales are extensively used in clinical and research settings to measure subjective phenomena and have been found to be valid and reliable [62]. Pain catastrophizing is measured using a well-validated two item measure rated on a 0–6 scale [63]. Pain acceptance is measured using two items from the Chronic Pain Acceptance Questionnaire (CPAQ), the only well-validated measure of pain acceptance [64]. The two CPAQ items were chosen based on their high loadings on each of the CPAQ’s two subscales, willingness to experience pain and engaging in activities despite pain [65].

#### Treatment expectations

We will examine treatment expectations using the 9-item Outcome Expectations for Exercise Scale, in which participants are asked to rate their agreement with potential benefits of physical activity measured on a 5-point Likert-type scale, with 1 indicating no expectations and 5 the highest expectations for exercise. Validity and reliability has been previously established for this measure [66].

#### Safety

Study participants are monitored weekly during the intervention period for the occurrence of adverse events, and at each assessment (baseline, post-treatment, 3 months follow-up, and 6 months follow-up). An adverse event is defined as any unfavorable and unintended diagnosis, symptom, sign (including an abnormal laboratory finding), syndrome or disease which either occurs during the study, having been absent at baseline, or if present at baseline, appears to worsen. Adverse events are recorded regardless of their relationship to the study intervention. Solicited adverse events include psychological distress (HADS score ≥ 15), and heart rate, blood pressure, and oxygen saturation collected during the 6-min Walk Test. In addition, information about muscle soreness is collected at each session of the yoga intervention.

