### Adherence and retention strategies

Adherence and retention are crucial determinants of the quality and interpretability of clinical trials. Obstacles to treatment attendance when intervening with patients with advanced disease include a variety of illness-related issues, such as unpredictable worsening of symptoms, limited energy, and alternate patient priorities given shortened life expectancies. Strategies we have implemented to boost attendance are among the best practices used in many high quality behavioral intervention trials. These strategies include motivational interviewing during the recruitment phase, weekly reminder emails during the intervention phase, prompt calls from interventionists to participants who missed a class, and make up sessions. Adequate adherence in this trial has been defined as 70% of the participants attending full sessions (120 min each) for at least 4 of the 8 treatment sessions. This is a revision from the initial definition of adequate adherence, which specified 70% attendance of at least 7 intervention sessions. We believe that the revision represents a more reasonable expectation given the severity of illness in this patient population. In reviewing data from three previous studies of the 8-session Mindful Yoga intervention, it was apparent that the goal of 70% of participants attending at least 7 sessions was likely overly ambitious [32, 33, 44]. This was achieved in only one of the three previous studies, with a population of much healthier women who were post-treatment for early stage breast cancer [32].

Attrition is a recognized challenge in studying the MBC population, given the progressive nature of the disease. To minimize missing data, we developed a retention plan to ensure minimal dropout due to reasons other than death or severe disease progression. This plan has featured minimization of participant burden, provision of participant support through the intervention protocols, solicitation of information about participant difficulties and prompt response to concerns raised, and consistent efforts to optimize the participants’ experience of study participation. Continuous quality monitoring of retention key performance indicators has allowed us to rapidly identify and respond to problems.

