### Randomization

Participants are randomized with a 2:1 allocation to: (a) Mindful Yoga, or (b) a support group control intervention. The study statisticians ([name] & [name]) generated the randomization scheme prior to the start of recruitment, which is kept in a study database which is not accessible by blinded study personnel. The study coordinator who executes the randomization schedule does not have access to the data and is not involved in the outcome assessments.

Due to the group nature of the interventions, enrollment has proceeded in cohorts. Randomization has been stratified within each cohort using variable block sizes of 3 and 6. The study coordinator informs each participant of their assigned treatment condition following the baseline assessment and ≤ 14 days prior to the start of the interventions.

We planned to conduct cohorts of 20–25 participants, so that each intervention group (two yoga groups and one social support group per cohort) would have between 5 and 10 group members. After the first two cohorts, we found that class size was an important factor in the yoga classes, which functioned best with at least five patients in attendance, but that class size did not appear to impact the functionality of the social support classes. Given that attendance at each class is usually less than 100%, it is necessary to assign at least seven patients to each yoga class to meet the expectation of usually having at least five patients in attendance. This necessitates enrolling at least 20 patients per cohort to fill two yoga classes and one social support class.

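### The dedicated muscle soreness question is tied to yoga sessions, so the solicited soreness rate depends on attendance and has no counterpart in the control arm

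*Protocol article*

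**What the plan says.** **The soreness question.** The Safety section lists the solicited events: a HADS threshold, and heart rate, blood pressure and oxygen saturation taken during the walk test. It then adds that "information about muscle soreness is collected at each session of the yoga intervention". Soreness is therefore the only solicited physical harm that is specific to yoga. No similar question is described for the social support sessions.

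**General monitoring.** The same section says "Study participants are monitored weekly during the intervention period for the occurrence of adverse events, and at each assessment". The definition is broad: "An adverse event is defined as any unfavorable and unintended diagnosis, symptom, sign" and so on, either new or worse than at baseline. There is no causality filter: "Adverse events are recorded regardless of their relationship to the study intervention". Table 1 marks adverse events at every point from baseline to 6 months.

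**Attendance.** The Randomization section plans class size around absences: seven or more women are allocated to a yoga class so that five or more will usually be present. Under Adherence and retention strategies, worsening symptoms and limited energy are named as obstacles to attendance, adequate adherence is set at 4 of 8 sessions, and the response to absence includes "prompt calls from interventionists to participants who missed a class, and make up sessions".

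**Practice outside class.** Under Mindful Yoga Program, "Participants are encouraged to practice yoga techniques at home", for 15–30 min on 5–6 days a week.

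**The concern.** A harm question asked only at the session is answered only by women who come. Soreness can be a reason not to come, so whether the harm is recorded by this route may depend on the harm itself. The yoga-arm rate from the question then describes attended sessions and not the whole programme as assigned.

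Two further limits follow from the same sentence. The question stops with the eight sessions, so later soreness has no solicited item. And because it is described for one arm only, any comparison of soreness between arms sets prompted plus general reporting against general reporting alone.

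At stake is the tolerability description. The article presents this as the first known randomized trial of yoga in advanced cancer and asserts that the poses carry no more risk of injury than everyday activities. The soreness question is the item best placed to check that assertion. No primary outcome, secondary outcome or feasibility criterion uses it, so the trial's main conclusions are not affected.

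**Working it through.** The article states no soreness rate, so there is no figure to reproduce. Two things can be checked: how far the question reaches, and whether the direction of any bias is determined.

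**1. Inputs**
- Target enrolment about 65, allocation 2:1 (Sample size; Randomization): 65 × 2/3 ≈ 43 yoga women, leaving about 22 controls.
- Eight weekly sessions: 43 × 8 = 344 yoga woman-sessions.
- Working class size: at least 7 assigned so that usually at least 5 are present (Randomization).
- Feasibility bar: at least 70% of patients attending at least 4 of 8 sessions (Statistical analysis).

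**2. Reach of the session-based question, before make-up sessions**
- At 5 of 7 present: 5/7 = 71% reached and 2/7 = 29% not reached, or 344 × 2/7 ≈ 98 woman-sessions. This is a class-filling ratio used as a stand-in for attendance, not an attendance rate stated by the plan.
- Floor at the bare feasibility bar: 70% of 43 is 30.1, so 31 women. If these 31 attend exactly four sessions and the other 12 none (an assumption), 31 × 4 = 124 of 344 = 36% are reached and 64% are not.
- Control arm: 22 × 8 = 176 woman-weeks, with no soreness question described.
- After session 8: the assessments at weeks 9, 21 and 34 have adverse-event recording but no soreness item described.

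**3. Direction of bias in the yoga-arm rate**

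Let *a* be the share of woman-sessions attended, *p*₁ the soreness rate in attended weeks and *p*₀ the rate in missed weeks. Then

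recorded − true = *p*₁ − [*a p*₁ + (1 − *a*) *p*₀] = (1 − *a*)(*p*₁ − *p*₀).

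The sign depends only on whether *p*₀ is above or below *p*₁. With *a* = 5/7 and an assumed *p*₁ of 20%:

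| Assumed *p*₀ | True rate | Recorded − true |
|---|---|---|
| 40% (soreness keeps women away) | 0.714 × 0.20 + 0.286 × 0.40 = 25.7% | −5.7 points |
| 20% | 20.0% | 0 |
| 10% (a missed class means fewer postures) | 0.714 × 0.20 + 0.286 × 0.10 = 17.1% | +2.9 points |

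Both directions are plausible. All these rates are assumptions, and the article offers nothing with which to choose among them.

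**4. Do other instruments fill the gap?**
- The daily diary has items on pain, fatigue, mood, catastrophizing and acceptance. It has no soreness item and runs only in alternate weeks.
- General adverse-event monitoring does cover new or worse soreness. The article does not say how a woman who misses a session is contacted for that week's check. Table 1 places the treatment-period checks at visits 2 to 9, which are eight visits for eight sessions.
- The missed-class call is described as an adherence measure, with no mention of harms.

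**The case against.** The strongest case is that the safety net already exists. Weekly monitoring is not stated to depend on attendance, it covers any new or worse symptom whatever the cause, and it continues at post-treatment, 3 and 6 months. The soreness question comes on top of it. How the weekly check is carried out is detail that an article may leave to the full protocol.

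Most of this stands, and it rules out several stronger readings that a reader might infer:

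- *That soreness in absent women, or after session 8, is not counted.* The Safety section and Table 1 show a route for recording it. What is missing is the dedicated question, not all recording.
- *That soreness from home practice is excluded.* Nothing limits the question to soreness caused in class, and an attending woman can report it at her next session. Nor does the article show that home practice outweighs class. Home time is 15 × 5 = 75 to 30 × 6 = 180 min a week, but it is not split by technique. Postures are 40 of the 75 class minutes given to postures, breathing and meditation. The same mix at home would give 40 to 96 min of postures, so the low end equals the class amount, and home practice is only encouraged.
- *That yoga-related harm is understated.* The table in the working shows that the sign depends on assumed rates. Between arms, asking only the yoga participants could inflate yoga's apparent excess.
- *That 29% of soreness records will be lost.* The 5-of-7 ratio is a planning rule, make-up sessions reduce the gap, and a woman may be asked about the missed week when she returns.

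What the objection does not remove is that the protocol itself chose to ask about soreness specifically, beyond general monitoring. That chosen item, as described, reaches attenders in one arm for eight sessions.

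**Conclusion.** The point holds in a limited form and is minor. The solicited soreness rate is conditional on attendance at yoga sessions, which soreness may itself reduce. It ends with session 8 and is not comparable between arms.

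The share of yoga woman-sessions outside the question is about 29% if the class-filling ratio is taken as attendance, and up to 64% at the bare feasibility bar if the remaining women attend nothing. Both figures are before make-up sessions and apply to this question only, not to adverse-event monitoring as a whole. The direction and size of any bias cannot be computed from the article, so it would be wrong to report that yoga-related harm is understated. The conclusion assumes that the full protocol does not already put the question to absent women and to the control arm.

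**What to change.** 1. In the call interventionists already make after a missed class, ask the same soreness question. Word it as *since the last session, including home practice*, and ask whether soreness was the reason for the absence.
2. Put the same item on the existing adverse-event form for both arms, at the weekly checks and at post-treatment, 3 and 6 months. On that shared form, phrase the home-practice clause neutrally (for example, *including activity at home*) so that it does not reveal the arm to masked staff.
3. Report the yoga-arm soreness rate over all scheduled weeks, and state how many weeks were not ascertained. Base any between-arm comparison only on the item asked in both arms.

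The cost is one question on an existing call and one on an existing form. Design, endpoints and sample size do not change. The reported soreness rate may change slightly.

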### Statistical analysis

The primary outcome related to feasibility is attendance, which is measured weekly at each intervention session. Adequate feasibility will be indicated by at least 70% of patients attending ≥ 4 of 8 sessions. The primary outcome related to acceptability is quantified by the Client Satisfaction Questionnaire-8 as assessed at the post-intervention evaluation. Adequate acceptability of the yoga intervention will be indicated by ≥ 80% of participants reporting a mean satisfaction score ≥ 3. Secondary outcomes are measurements of change at the post-treatment, 3-month follow-up, and 6-month follow-up evaluations in pain, fatigue, sleep quality, psychological distress, mindfulness and functional capacity. These will be analyzed both as individual time points and in longitudinal analyses. Treatment expectations—including potential pre-randomization selection biases regarding the yoga intervention—will be controlled in analyses with the data from the measure assessing outcomes expectations [66]. We will apply the intent-to-treat assumption for all analyses.

We will also explore within-person associations between yoga practice, outcomes (pain, fatigue, mood) and mediators (pain catastrophizing, pain acceptance) among participants in the yoga condition. Multilevel random effects models will be used to evaluate these associations, with individuals’ mean levels of yoga practice as a control variable, and practice rates person-centered to control for potentially spurious within-person associations [67]. Multilevel modeling is an advanced methodology for integrating data from multiple levels of sampling, such as this study’s two levels (within-persons and between-persons). Multilevel models are particularly advantageous in analyzing data sets with many repeated measures, such as daily diary records [68, 69]. By preserving the rich detail in each individual’s full data set, multilevel models allow for a sensitive independent determination of day-to-day interrelated happenings for each patient, as well as aggregation of individual estimates for reliable results for the average patient. Multilevel models also enable strict control for potential confounds, such as serial autocorrelation in measurements.

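### The yoga-arm diary model guards the within-person practice slope only by person-centring, which leaves the weekly class day in it; depending on how diary practice is defined, the slope can be inflated, reversed or unaffected

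*Protocol article*

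**What the plan says.** The diary analysis is set out in the second paragraph of Statistical analysis: "We will also explore within-person associations between yoga practice, outcomes (pain, fatigue, mood) and mediators", "among participants in the yoga condition". The named practice terms are multilevel, "with individuals’ mean levels of yoga practice as a control variable, and practice rates person-centered to control for potentially spurious within-person associations". On other confounders the section makes one general remark: "Multilevel models also enable strict control for potential confounds, such as serial autocorrelation in measurements".

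Under Mindful Yoga Program: "This intervention consists of eight 120-min weekly group sessions led by a certified yoga instructor". On content: "Each session includes gentle postures (approx. 40 min), breathing techniques (10 min), meditation (25 min"), followed by 20 min of presentation and 25 min of group discussion. Separately, "Participants are encouraged to practice yoga techniques at home", for 15–30 min on 5–6 days a week.

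Study Design and Measures say that diaries are kept on alternate weeks, four weeks in all, and cover symptoms and, in the yoga arm, yoga practice. Neither says whether class time is included or whether the item is minutes or yes/no. Under Attendance, entry and exit times are recorded at every session. For the support arm, "The scheduling of the sessions is identical to that for the yoga intervention".

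**The concern.** Person-centring is offered as protection against spurious within-person associations, but it protects only against stable differences between women. The class is a day-level event. On one day in seven a woman gets a large dose of yoga techniques together with two hours of company, instruction and discussion. If symptoms differ on that day for any reason, and recorded practice also differs on that day, the practice slope absorbs the difference.

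Group contact is one of the things the support arm was chosen to control for. The diary analysis uses the yoga arm alone, so that control is not available in it. Study Design presents the daily measures as a rigorous test of two mediators, and the Discussion promises a first systematic evaluation of mechanisms. What is at stake is therefore a mechanism claim: lower pain or catastrophizing on class days could be reported as an effect of practising yoga.

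**Working it through.** **Inputs from the article.** Session components: 40 + 10 + 25 + 20 + 25 = 120 min, which reproduces the stated session length. Techniques take 40 + 10 + 25 = 75 min; talk and discussion take 20 + 25 = 45 min. Home practice is 15–30 min on 5–6 days. Diary days: 4 weeks × 7 = 28, assuming one class in each diary week. Yoga arm: 65 × 2/3 ≈ 43 women.

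**Class-day share of within-person variation.** Let d₁ be the class day's deviation from the weekly mean and SS the sum of squared deviations over seven days. The share is d₁²/SS. The R² of a class-day indicator is 7/6 times that share, because the other six days average −d₁/6 and d₁² + 6(d₁/6)² = (7/6)d₁².

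*Class minutes counted*
- 75 min in class, 30 min on five days, 0 on one: mean 225/7 = 32.1, d₁ = 42.9, SS = 2,893. Share = 1,837/2,893 = 63%; R² = 74%.
- 75 min in class, 15 min on six days: mean 165/7 = 23.6, d₁ = 51.4, SS = 3,086. Share = 2,645/3,086 = 86%; R² = 100%.
- All 120 min counted: share 78–86%.

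*Yes/no item, class day scored as practised*
- Five of seven days: d₁ = 2/7, SS = 70/49. Share = 4/70 = 5.7%; R² = 6.7%. With six of seven days, R² = 2.8%.

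*Home minutes only*
- Skipped on class day, 15 min on five days: mean 75/7 = 10.7, d₁ = −10.7, SS = 321. Share = 115/321 = 36%; R² = 42%, with d₁ now negative. With six days, R² = 100%.
- Unrelated to class day: R² about 0.

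**Size of the false slope.** If class day shifts the symptom by δ and practice does nothing, the expected slope in a fixed week is δ·d₁/SS. For the first pattern and a 1-point fall: −42.9/2,893 = −0.0148 per min, or −0.44 points per 30 min. When home minutes vary, home practice can also fall on class days and attendance is 50–100%, simulation gives −0.30 to −0.35 per 30 min with 75 class minutes counted and −0.22 to −0.24 with 120.

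**False-positive rates.** Assumptions: 43 women, 28 days, 70% class attendance, autocorrelation 0.3, no practice effect, nominal 5%. Ranges are over repeated simulations that differed in how often home practice was done.

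| What counts as practice | Class-day effect 0.2 SD | 0.3 SD |
|---|---|---|
| Class minutes (75) plus home | 43–48% | 76–80% |
| Home only, skipped on class day (sign reversed) | 13–20% | 22–36% |
| Yes/no, class counted | 6–9% | 8–11% |
| Home only, unrelated to class day | about 5% | about 5% |

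Adding a class-attended-today indicator brought the error back to about nominal in every row.

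**The case against.** The strongest reply is that this argues from silence. The article condenses a fuller protocol, no analysis plan is shown, and the remark on confounders is open-ended. Day-level covariates of an exploratory model are often left to the analysis plan. That stands as far as it goes: the absence of a list of covariates is no fault. But the article does specify the exposure terms and what they are meant to protect against, and that protection does not reach a class-day effect. Neither does modelling autocorrelation.

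A second reply is that the diary item may well record home practice only, since attendance is logged separately, home practice is described as its own activity, and the section speaks of practice rates. This also stands. A reader might infer that the slope is largely a class-day contrast whatever the definition, or that bias arises even if home practice is random across days. The documents do not support either inference: the first needs class minutes to be counted, and the second fails because random home practice is uncorrelated with class day. A warning that practice would appear harmful likewise depends on home practice being skipped on class days, which the article does not say.

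Third, a better class day may be a genuine effect of 75 min of yoga techniques, so removing it is partly a choice of question. That is right, and it argues for reporting the class-day effect openly rather than for making home practice the only exposure.

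**Conclusion.** The point holds conditionally. Person-centring cannot keep a weekly class effect out of the practice slope, and the article leaves the exposure undefined on the feature that decides whether this matters. The bias is large if class minutes count. It is of opposite sign, with lower false-positive rates in the simulations, if home practice alone counts and is skipped on class days. It is small for a yes/no item at class-day effects of 0.2–0.3 SD and absent if home practice is unrelated to class day.

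The class-day effect sizes, 70% attendance, autocorrelation and a full 28 diary days are assumptions. The article does not say when in the day diaries are completed or whether the models are same-day or lagged, and either could change the size. It would be wrong to infer that the trial's main conclusions are at risk: the primary feasibility and acceptability outcomes and the randomized comparison do not use this model. This is a cheap improvement to an exploratory analysis.

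**What to change.** In Statistical analysis:

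1. State whether diary practice includes class time, and in what unit it is recorded.
2. Add a class-attended-today indicator, taken from the sign-in log, to the diary models. Alternatively, report the slope on non-class days beside the unadjusted slope.
3. Report the class-day effect separately, and compare it descriptively with the session-day effect in the support arm's diaries, which cover the same symptoms on the same session schedule.

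No new data are needed. The cost is some precision in the practice slope, because class days no longer drive it, and a narrower meaning: the adjusted slope describes practice outside class. Reporting both slopes keeps the broader question visible.
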